### Exclusion criteria

We will exclude individuals who are pregnant, lactating, or postmenopausal; professional athletes or individuals undergoing changes in the intensity and frequency of their physical activities throughout the last month; individuals with a confirmed clinical history of eating disorders, gastrointestinal diseases, cardiovascular, hepatic, renal, pulmonary, or endocrine diseases (such as thyroid conditions or diabetes), cancer, or any severe acute or chronic disease; current smokers, drug or alcohol addicts; those with known allergies or sensitivities to supplement or placebo components; individuals with a history of bariatric surgery; those who skip at least one meal; individuals on special diets, such as vegetarian diets; those with a regular intake of more than 300 mg of caffeine or more than 30 g of fiber per day; those adhering to a calorie-restricted diet for three months prior to the start of the study; individuals who routinely consume pre-, pro-, and synbiotic products; those who take antibiotics for one month before the study begins; or individuals using medications, including cholesterol and lipid-lowering drugs (e.g., statins), blood sugar-lowering drugs (e.g., insulin, metformin, liraglutide), antihypertensive medications, drugs affecting GI function, weight, body composition, or appetite (e.g., antipsychotics, corticosteroids, anti-obesity drugs, oral contraceptives, antidepressants), weight loss supplements (including those affecting appetite, metabolism, or food absorption) such as orlistat, and drugs interacting with green tea (e.g., digoxin, tacrolimus, warfarin).

Participants will be excluded from further analysis if they opt out, use antibiotics or other pre-, pro-, and synbiotic products, or meet the exclusion criteria anytime during the study, or do not comply with their assigned treatment regimen during the study.

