### Strategies to improve adherence to interventions {11c}

Our strategies for increasing adherence to the intervention protocol include regular follow-ups through monthly in-person visits to review supplement use, dietary compliance, and symptom logs, along with weekly phone calls to monitor supplement use and adherence to the assigned intervention. Nutritionists will offer free counseling support, providing personalized feedback and motivation during these visits as an incentive. We will measure adherence through return rates, checklist completion, and self-reported logs. If participants miss more than 20% of doses, we will schedule a counseling session to address any barriers to adherence.

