### Methods in analysis to handle protocol non-adherence and any statistical methods to handle missing data {20c}

All analyses will follow the intention-to-treat (ITT) principle. Missing data will be addressed using multiple imputation under the assumption of missing at random (MAR). Anthropometric measures, body composition variables, blood pressure, biochemical indices, and questionnaire scores will be included in the imputation model using a fully conditional specification (FCS) approach. In addition, sensitivity analyses will be performed with complete cases to confirm the robustness of the results.

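### The rule dropping randomised participants from analysis after post-randomisation events contradicts the protocol's intention-to-treat commitment

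*Protocol article*

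**What the plan says.** The protocol article gives two rules on who is analysed.

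- **Exclusion criteria, last paragraph.** "Participants will be excluded from further analysis if they opt out, use antibiotics or other pre-, pro-, and synbiotic products". Two more groups are then named. One is people who become ineligible after entry ("or meet the exclusion criteria anytime during the study"); the other is people who fail to adhere ("or do not comply with their assigned treatment regimen during the study"). That makes four kinds of event, all of which can occur after randomisation.
- **Section {20c}**, whose heading covers both non-adherence and missing data. "All analyses will follow the intention-to-treat (ITT) principle". Missing values are to be multiply imputed under missing at random (MAR), by fully conditional specification. The one sensitivity analysis is on complete cases: "sensitivity analyses will be performed with complete cases to confirm the robustness of the results".

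Two further sections bear on the point. Section {11b} sets out when product is stopped and names gastrointestinal and allergic reactions caused by the supplement. Section {22} says that participants in whom adverse effects are found will be taken out of the study after consultation. It does not say whether their data are still analysed.

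**The concern.** Intention-to-treat means that everyone randomised is analysed in the arm assigned, whatever happens afterwards. A rule that takes out people who leave, use a prohibited product, acquire an exclusion criterion or fail to adhere is the reverse of that. Both are written as firm statements about the same trial, and neither refers to the other.

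Two things are at stake. First, the set for the primary comparison is not fixed, so it could be settled once results are visible. Secondly, if the removal rule is the one applied, the arms compared are no longer the arms randomised. Leaving the trial and failing to adhere can both follow from how a person tolerates the product, so those removed may differ between arms in number and in kind.

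**Working it through.** The protocol has no figure on this point to reproduce. The check is to take each kind of participant and apply each rule.

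| Participant | Exclusion criteria, last paragraph | {20c}, main analysis | {20c}, complete-case analysis |
|---|---|---|---|
| Non-adherent, measured at week 8 | out | in, observed data | in |
| Used antibiotics or pre-/pro-/synbiotics, measured at week 8 | out | in, observed data | in |
| Met an exclusion criterion on study, measured at week 8 | out | in, observed data | in |
| Opted out, no week-8 data | out | in, imputed | out |
| Taken out for adverse effects under {22}, no week-8 data | not stated | in, imputed | out |

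**Step 1: do the rules conflict?** Yes. In the first four rows the second and third columns disagree.

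**Step 2: does the complete-case analysis reconcile them?** No. It agrees with the removal rule only in the fourth row. Anyone in the first three rows has complete data and stays in.

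**Step 3: could the removal rule mean stopping product or visits, not analysis?** The wording is about analysis, and stopping product has its own section, {11b}.

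**Step 4: could the removal rule define a per-protocol set?** No section names such a set, and {20c} claims every analysis for intention-to-treat.

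**Step 5: what bias could follow?** For arm *a*, let *p_a* be the share removed, and let *K_a* and *R_a* be the mean outcome change in those kept and those removed.

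- Mean as randomised: *M_a* = (1 − *p_a*)·*K_a* + *p_a*·*R_a*.
- Hence *K_a* − *M_a* = *p_a*·(*K_a* − *R_a*).
- Writing S for supplement and P for placebo, the bias in the between-arm difference under the removal rule is *p_S*·(*K_S* − *R_S*) − *p_P*·(*K_P* − *R_P*).

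This is zero only if nobody is removed, if those removed resemble those kept, or if the two terms cancel. The protocol gives none of the six quantities. Neither the size nor the sign can be worked out from it.

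**The case against.** The strongest reply is that {20c} already promises the right analysis under the heading where a reader would look for it. On that view the sentence in Exclusion criteria is loose drafting that an analysis plan will override. A plan may indeed do so, but this is not a detail left for later. The document states two incompatible rules, and one must be withdrawn.

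Other points have some force.

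- **Blinding.** Section {17a} keeps data analysts blind to allocation, which limits a choice of set made to suit the result. The protection is partial, since arms coded A and B still show a difference.
- **Withdrawn consent.** Someone who leaves may refuse further follow-up. This concerns only part of one of the four groups.
- **Imputation is not a full cure.** If people leave because of side effects and have no later data, MAR is itself doubtful. The gain from {20c} is clear for those who are still measured and less certain for those who are not.

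A reader might also infer more than the document supports.

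- *That the counselling rule in {11c} is a second contradiction.* It reads: "If participants miss more than 20% of doses, we will schedule a counseling session to address any barriers to adherence". This triggers adherence support and does not define non-compliance for analysis, so it can stand beside a separate definition. A numeric cut-off is commonly left to the analysis plan.
- *That people who become more active as advised would be removed.* The criterion "individuals undergoing changes in the intensity and frequency of their physical activities throughout the last month" stands in a screening list and is naturally read as the month before enrolment.
- *That {11b} is defective because it does not list pregnancy, lactation or interacting drugs as reasons to stop product.* Its criteria are general, and an article need not list every case.
- *That the trial loses a definite amount of power.* Any figure would rest on assumed removal shares. The removals may also fall within the 20% dropout allowance in the sample size section.

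**Conclusion.** The contradiction is real and stands on the text alone. As written, the removal rule would select the primary analysis set on events after randomisation that the supplement may influence. The harm is qualitative: possible bias of unknown size and sign, and an analysis set that is not fixed.

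The conclusion that bias is possible assumes that at least one of the four events is related both to the arm and to outcome. Section {11b} makes the link to the arm plausible, but the document gives no data that would establish it. The conclusion that the two rules conflict needs no assumption. The point should be corrected before unblinding. It does not make the trial unsound, since the appropriate analysis is already in {20c}.

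**What to change.** 1. Amend the last paragraph of Exclusion criteria so that the four events may end product use but not inclusion in the analysis. All randomised participants are analysed in their assigned arm under {20c}. Data already collected are kept, the existing week-8 visit is held where the participant consents, and missing outcomes are imputed. Note that MAR is weaker for those who leave because of side effects.
2. State in {22} that the same rule covers participants taken out for adverse effects. Otherwise the route most likely to depend on the arm stays open.
3. Keep the removals, if wanted, only as a labelled per-protocol sensitivity analysis, distinct from the complete-case analysis, with the compliance threshold fixed before unblinding.

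**Cost.** A few sentences, with the ethics approval and registry entry that {25} requires. No extra participants are needed, but the final visit must now be held for people who would have been removed. Some loss may be past repair. Recruitment began on June 22, 2025, so the first 8-week course (56 days) could end on August 17, before the current version of September 5, 2025. Week-8 data may already be missing for participants removed before an amendment; whatever was collected can be restored.

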### Who will take informed consent? {26a}

One of the research team members will be assigned to obtain informed consent from participants or their authorized representatives. To do this, a detailed ethics committee-approved consent form that explains the study’s purpose, procedures, risks, benefits, and the participant’s right to withdraw at any time will be provided to the participants in an understandable language and manner, allowing ample time for questions. Both the participant and the person obtaining consent will sign and date the document, and copies will be kept in trial records and given to the participant. We will only request surrogate consent if the participant has a disability.

### Additional consent provisions for collection and use of participant data and biological specimens {26b}

As part of this study, we will securely store de-identified participant data and blood samples in a coded form for potential use in future research that receives ethics committee approval and aligns with the original study’s ethical framework. These data and specimens will be stored at Mashhad University of Medical Sciences under strict confidentiality rules, accessible only to authorized researchers with ethics clearance. Participants can still opt out of future use of their data or specimens for other studies without affecting their current participation or rights, and they can request that stored materials be destroyed at any time. We may share anonymized data with other institutions for scientifically validated research upon institutional approval, but we will not disclose any personally identifiable information. Participants will not receive financial benefits from commercial uses of research findings (like patentable discoveries) unless required by law. We will publish all research outcomes in aggregate form to ensure confidentiality. If we want to recontact participants for additional studies, we will do so only under a separate ethics-approved protocol, with prior notice and consent options.

## Interventions

### Explanation for the choice of comparators {6b}

A placebo was chosen to isolate the effects of the supplement on the outcome variables. This approach enables a controlled evaluation of changes solely caused by the investigational supplement. The placebo will be given with identical appearance features to maintain participant blinding.

### Intervention description {11a}

A hypocaloric diet (500 kcal deficit) consisting of 50% carbohydrates, 20% protein, and 30% fat will be prescribed for participants in both groups. Total energy expenditure will be calculated based on the Mifflin equation. Participants will be encouraged to engage in 150 min of physical activity per week.

This study will utilize a supplement consisting of pasteurized *Akkermansia muciniphila*, green tea extract, and glucomannan konjac, offered in 2-g sachets. The placebo is formulated with microcrystalline cellulose and also comes in 2-g sachets. Participants will be instructed to consume one sachet 30 min before every meal (breakfast, lunch, and dinner) for 8 weeks. Parsi Lact Company (Shiraz, Iran) prepared and packaged the supplements and placebos in sachet form. Both the placebo and the supplement exhibit the highest level of similarity, and the containers will remain unlabeled and coded as A or B to ensure both researchers and participants are unaware of the type of intervention they will receive. Each participant will receive a monthly supply of the sachets they need for consumption over the course of a month. To promote sachet consumption, participants will receive weekly calls and briefing messages. Compliance will be tracked by counting the monthly returned used and unused sachets. Additionally, we will assess sachet consumption through food recalls. At the beginning of the study, all participants will complete a checklist to collect their general characteristics, medical history, and information regarding medications and supplements they are currently using.

### Criteria for discontinuing or modifying allocated interventions {11b}

For safety concerns, if a participant experiences severe or ongoing adverse effects (like unmanageable stomach symptoms or allergic reactions) due to the supplement, intervention will be stopped after discussing with a physician. The criteria for stopping or changing the assigned interventions include: (1) Safety concerns, such as severe adverse events (like anaphylaxis or severe gastrointestinal symptoms) or persistent intolerable reactions. (2) If a participant requests to stop at any time, their request will be *honored without consequence. (3) If a participant’s** condition worsens, requiring the intervention to be terminated.*

### Strategies to improve adherence to interventions {11c}

Our strategies for increasing adherence to the intervention protocol include regular follow-ups through monthly in-person visits to review supplement use, dietary compliance, and symptom logs, along with weekly phone calls to monitor supplement use and adherence to the assigned intervention. Nutritionists will offer free counseling support, providing personalized feedback and motivation during these visits as an incentive. We will measure adherence through return rates, checklist completion, and self-reported logs. If participants miss more than 20% of doses, we will schedule a counseling session to address any barriers to adherence.

### Relevant concomitant care permitted or prohibited during the trial {11d}

Participants can take routine supplements like multivitamins within the dietary limits that do not affect the study outcomes. However, specific interventions are prohibited to maintain the trial’s integrity, including the use of prebiotic, synbiotic, and probiotic supplements and products. Participants are also prohibited from taking other weight-loss supplements, herbal products, or obesity medications, or participating in other conflicting clinical trials.

### Provisions for post-trial care {30}

According to informed consent, if any physical or mental problems occur to the participant during or after the research related to this research, the treatment of complications, their costs, and related compensation will be the responsibility of the supporting body.

### Outcomes {12}

#### Primary outcomes

##### Anthropometric measurements and assessment of body composition

In this study, the height and weight of participants will be recorded using standardized methods. Height will be measured with a wall-mounted stadiometer (Seca 206, Germany) to the nearest 0.1 cm, while weight will be taken with a digital floor scale (Seca 813, Germany) to the nearest 0.1 kg. Measurements will be obtained without shoes and in minimal clothing to ensure precision. The body mass index will be calculated by dividing the weight in kilograms by the square of the height in meters. Waist circumference will be measured using a flexible, non-stretchable tape measure at the midpoint between the bottom of the rib cage and the iliac crest, with participants standing upright, feet close together, and without any pressure applied. This measurement will be recorded to the nearest 1.0 cm. Hip circumference will be taken at the largest part of the pelvis using a non-stretchable tape. The waist-to-hip ratio will be computed using the appropriate formula. Body composition will be analyzed using the Tanita-MC780 body composition analyzer (Tanita Corporation, Tokyo, Japan). Instructions for participants before assessing body composition will be provided based on the manufacturer's suggestions (tanita.co.uk/mc-780ma-p). The instructions included abstaining from eating and drinking for three hours before performing the analysis, avoiding exercise and alcohol intake for at least 22 h, avoiding excess fluid intake 24 h before the analysis, and emptying the bladder before performing the analysis.

### Secondary outcomes

## Biochemical assessment

Biological specimens will be collected during the study. At both the start and conclusion of the study, 10 cc blood samples will be taken from all participants who have fasted for 12 h. Serum samples will be prepared by centrifuging the blood samples at 2500 rpm for 15 min and will be promptly stored at −20 °C until they are analyzed. The levels of fasting blood glucose, triglycerides, total cholesterol, high-density lipoprotein cholesterol, and low-density lipoprotein cholesterol will be assessed using the Biotecnica Instrument 1500 (BT 1500) analyzer and MAN, a commercial kit, following the guidelines provided by the manufacturer. Associated indices such as TYG, TC-HDL ratio, and FBS-HDL ratio will also be determined.

## Blood pressure measurement

Blood pressure will be measured at the start and end of the study. Participants’ systolic and diastolic pressures will be taken twice in the left arm with a digital device, allowing a 5-min interval between measurements. This happens while sitting following a 15-min break with a snug cuff. To ensure accuracy, participants must refrain from smoking, consuming coffee, or engaging in heavy exercise for 30 min before measurements. The average of the two readings will determine blood pressure.

## Assessment of appetite

The Visual Analogue Scale (VAS) in its online format will be utilized to evaluate subjective feelings of appetite. The VAS is a validated instrument that consists of a 100 mm horizontal line, marked with words at both ends that indicate the extremes of satiety, fullness, hunger, and prospective food consumption (PFC), along with the urge to eat sweet, salty, or fatty foods [21]. All patients will complete the VAS at the beginning, middle, and end of the study. The timing of the VAS assessments will occur before consumption of the sachet or meal, and at 30 min, 1 h, and 2 h after each meal.

### Further measurements

## Assessment of dietary intakes and physical activity levels

This study will evaluate dietary consumption using a three-day 24-h dietary recall, which will consist of two weekdays and one weekend, at the starting point and at the end of the fourth and eighth weeks, through in-person interviews. Furthermore, food recalls will be evaluated to determine the average daily macro- and micronutrient intakes of participants using Nutritionist IV software (First Databank Inc.), which has been customized for Iranian foods.

The levels of physical activity will be assessed at the beginning, in the fourth week, and in the last week by utilizing the short version of the International Physical Activity Questionnaire (IPAQ), which has been confirmed as valid for the Iranian population [22]. This questionnaire includes seven items and collects information on the time spent doing vigorous, moderate, and light activities in the past week. The questionnaire also gathers information on hours spent sitting. The questionnaire provides the quantitative metabolic equivalent (MET) per week.

## Assessment of gastrointestinal symptoms

The Gastrointestinal Symptom Rating Scale (GSRS) questionnaire will be utilized to assess potential gastrointestinal symptoms [23]. The GSRS consists of 15 items that measure the presence and intensity of gastrointestinal symptoms across five categories: abdominal pain, constipation, diarrhea, reflux, and indigestion. Each item on the questionnaire is rated on a 7-point Likert scale, where a score of one signifies no symptoms and a score of seven represents severe and intolerable symptoms. The Persian version of this questionnaire has already been validated. Participants from both groups will complete the GSRS at the start, mid-point, and conclusion of the study.

### Participant timeline {13}

[figure not shown]

#### Sample size {14}

The sample size was calculated using the formula for the difference between two independent means, considering the mean and standard deviation of fat mass changes observed in the intervention (24.3 ± 1.8) and control (26.7 ± 2.8) groups as reported by D Roberts et al. [24]. With a type I error rate set at *α* = 0.05 and a statistical power of 1 − β = 0.90 aimed at detecting a standardized effect size of at least Δ = 0.80, the minimum required sample size for each group was determined to be 27 participants. However, after accounting for a potential dropout rate of 20%, this figure increased to 36 participants per group. Ultimately, a total of 72 overweight or obese adults will be recruited.

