## Statistical methods

### Statistical methods for primary and secondary outcomes {20a}

All statistical analyses will be conducted using SPSS software version 26. The primary outcome is the change in anthropometric measures and body composition parameters (body weight, BMI, waist circumference, hip circumference, waist-to-hip ratio, fat mass, fat-free mass, and visceral fat) from baseline to the end of the intervention. The secondary outcome includes (1) changes in systolic and diastolic blood pressure, (2) biochemical indices including fasting blood glucose, triglycerides, total cholesterol, HDL cholesterol, LDL cholesterol, TYG index, TC-to-HDL ratio, and FBS-to-HDL ratio, and (3) appetite parameters derived from the VAS questionnaire (satiety, hunger, fullness, prospective food consumption, and desire for specific foods). The primary outcome will be evaluated at a two-sided significance level of *p* < 0.05. To account for multiple secondary outcomes and reduce the risk of type I error inflation, the Benjamini–Hochberg false discovery rate (FDR) adjustment will be applied.

Baseline characteristics between the two study groups will be compared using independent t-tests (or Mann–Whitney *U* tests for non-normally distributed data) for continuous variables and chi-square tests for categorical variables. For within-group changes over time, paired t-tests (or Wilcoxon signed-rank tests) will be used. Between-group comparisons of changes in primary and secondary outcomes will be performed using repeated measures ANOVA or ANCOVA, adjusting for baseline values and potential confounders (e.g., age, sex, baseline BMI), provided model assumptions are satisfied. If assumptions are violated, appropriate non-parametric alternatives will be applied. Post-hoc tests with Bonferroni correction will be conducted when global tests indicate statistical significance.

The normality of continuous variables will be assessed using the Shapiro–Wilk test and by visual inspection of histograms and Q-Q plots. Homogeneity of variances will be checked using Levene’s test. These steps are essential to determine whether parametric or non-parametric statistical methods should be applied.

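### The planned 27 per group does not give 90% power for a standardised effect of 0.80 under the two-sided test; with the expected 29 analysed per group, power is about 85%

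*Protocol article*

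**What the plan says.** The section Sample size {14} of the protocol article describes its method: "The sample size was calculated using the formula for the difference between two independent means". The inputs it cites are "fat mass changes observed in the intervention (24.3 ± 1.8) and control (26.7 ± 2.8) groups", taken from a published study and given without a unit. The design values follow: "With a type I error rate set at *α* = 0.05", "a statistical power of 1 − β = 0.90", and the aim of "detecting a standardized effect size of at least Δ = 0.80". The result is that "the minimum required sample size for each group was determined to be 27 participants", and "after accounting for a potential dropout rate of 20%, this figure increased to 36 participants per group", which makes 72 in total. The section does not say whether alpha is one-sided or two-sided.

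Statistical methods {20a} does say: "The primary outcome will be evaluated at a two-sided significance level of" 0.05. It defines the primary outcome as change from baseline to the end of the intervention in a list of anthropometric and body composition measures that includes fat mass. Between-group comparisons are to use repeated measures ANOVA or ANCOVA with baseline adjustment. Sequence generation {16a} fills the 72 places with 12 blocks of 6.

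**The concern.** A reader will take 27 per group as the requirement for the test the protocol specifies, which is two-sided. For the stated effect size and power it looks too small by 6 or 7 per group. If so, the 90% claim fails at the target the protocol itself sets, and a null result would be read as coming from a trial with a 10% type II risk when the risk is nearer 15%.

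There is also a break between the inputs and the result. The quoted means and SDs do not lead to 0.80, and it is doubtful that they describe the endpoint to be analysed, which is change in fat mass. If they do not, the SD behind the calculation is not the SD that determines the trial's power.

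**Working it through.** **Inputs.** From Sample size {14}: alpha 0.05, power 0.90, d = 0.80, means and SDs 24.3 ± 1.8 and 26.7 ± 2.8, dropout 20%, 36 randomised per group. From Statistical methods {20a}: two-sided test. From Trial design {8}: 1:1 allocation.

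**Reproducing 27.** The normal formula for two independent means is n per group = 2(z_alpha + z_beta)² / d², with z_beta = 1.282 for 90% power.

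- One-sided 0.05: 2 × (1.645 + 1.282)² / 0.64 = 26.8, so 27 (t test: 28).
- Two-sided 0.05: 2 × (1.960 + 1.282)² / 0.64 = 32.8, so 33 (t test: 34).

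So 27 is matched by the one-sided normal formula at d = 0.80 and not by the two-sided one.

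**Do the quoted means and SDs give 27 instead?** The difference is 26.7 − 24.3 = 2.4. The pooled SD is √((1.8² + 2.8²)/2) = 2.354, so d = 2.4/2.354 = 1.02. At 90% power this needs 21 per group two-sided (t test 22) or 17 one-sided (t test 18). Using the larger SD alone, d = 2.4/2.8 = 0.86, which needs 29 two-sided (t test 30) or 24 one-sided (t test 25). None of these is 27. To turn a difference of 2.4 into d = 0.80, the SD would have to be 2.4/0.80 = 3.0, which is larger than either quoted SD.

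**Two-sided power at d = 0.80, unadjusted comparison.** The normal approximation is Φ(d√(n/2) − 1.960). The t-test column uses the noncentral t distribution.

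| Analysed per group | Normal | t test |
|---|---|---|
| 27 (stated minimum) | 83.6% | 82.2% |
| 29 (36 × 0.8 = 28.8) | 86.1% | 84.9% |
| 33 | 90.1% | 89.3% |
| 34 | 91.0% | 90.2% |
| 36 (no dropout) | 92.4% | 91.7% |

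By the t test, 90% is reached from 34 analysed per group. From 36 randomised, that allows a loss of 2/36 = 5.6%, not 20%. With 29 analysed, the effect detectable with 90% power is 0.87 (t test), or 3.242 × √(2/29) = 0.85 by the normal formula.

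**Dropout step.** 27/0.8 = 33.75, so 34 per group and 68 in total. Rounded up to full blocks of 6, 68 becomes 72, or 36 per group. The protocol does not give this reason, but the numbers fit it.

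**The figures described as changes.** If they are in kg (an assumption, since no unit is given), mean fat mass changes of 24.3 and 26.7 are very large for adults with a BMI of 27 to 34.9, the range in Eligibility criteria {10}. Read as losses, they would mean that the control group lost more. They look like fat mass levels. The SD of a level is in general not the SD of a change from baseline.

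**The case against.** Several points on the other side deserve weight.

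- **Origin of 27.** Since the section states no sidedness, a one-sided calculation is an inference. A two-sided t test at d = 0.90 also gives 27 (26.9), and the text speaks of an effect of at least 0.80. This stands as a caution about where 27 came from. It does not make 27 correct for two-sided 0.05, 90% and 0.80.
- **Larger effect on the quoted data.** At d = 1.02, 29 per group give about 97% two-sided power; at 0.86, about 89%. The choice of 0.80 may be a deliberately cautious target, so a gap between 1.02 and 0.80 is not in itself an error. But 0.80 is where the protocol claims 90%, and it does not explain how it got from one value to the other.
- **Baseline adjustment.** ANCOVA could recover power. If the correlation of baseline with the analysed outcome were 0.5, 29 per group would give about 93% at 0.80; at 0.3, about 88%. Both correlations are assumptions. The sample size section uses the unadjusted two-means formula and claims no such gain, so this does not rescue the stated figure. It does mean that 85% must be described as the power of an unadjusted comparison.
- **Multiple imputation.** The protocol plans it for missing data, but imputation does not in general restore the information in lost outcomes, and the section itself inflates for dropout.
- **Dropout step.** A reader might infer that 36 is a second arithmetic error because 27 with 20% dropout gives 34. The excess of 2 per group errs on the large side, adds power and fits whole blocks. It is not a material error.
- **Input figures.** A reader might go further and say that they cannot be changes, perhaps arguing from this trial's 500 kcal deficit over 8 weeks. The documents do not support that. The figures come from another study, its report is not available here, no unit is given, and this trial's diet places no bound on another study's results.

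**Conclusion.** The stated 27 per group is inconsistent with the protocol's own alpha, power, effect size and two-sided test, which together need 33 or 34. At a standardised effect of 0.80, an unadjusted two-sided comparison has about 82% power with 27 per group and about 85% with the 29 expected after 20% dropout. The shortfall against the stated 90% is therefore about 5 percentage points at the planned recruitment. These figures assume equal group sizes, a common SD, dropout as planned and no gain from covariates.

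The conclusion does not depend on how 27 was obtained, on the dropout rounding or on what the cited figures represent. On the last point, the supportable statement is that they are implausible as changes, give 1.02 and not 0.80, and are not tied to the SD of the change endpoint. A reader might also infer that the trial is too small to be worth running as planned. That does not follow: 85% at 0.80 is a usable design, and adjusted analysis may do better. What is wrong is the stated number.

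**What to change.** Keep 72 participants and revise the sample size paragraph:

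1. State that the calculation is two-sided.
2. Replace the power statement with wording such as: *With 36 randomised and about 29 analysed per group, an unadjusted two-sided 5% comparison has about 85% power for a standardised difference of 0.80, or 90% for 0.87.*
3. Check the cited source. Give the unit and the correct label of the two means and SDs, and say how they relate to 0.80. If they prove to be levels, use an SD of change instead.
4. Optionally, add a phrase explaining that 34 per group was rounded up to 36 to fill complete blocks of 6, if that was the reason.

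The cost is one paragraph and a less favourable power figure, with no extra participants and no change to the endpoint or analysis. Holding 90% at 0.80 after 20% dropout would instead require 33/0.8 = 41.25, so 42, or 34/0.8 = 42.5, so 43, randomised per group (84 or 86 in total). Trial status gives recruitment as open since June 2025 and due to end in October 2025, so restating the power is the proportionate course, preferably before results are known.
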